### ****3.2 Secondary Objectives****

**Secondary Objective 1:**
To evaluate the effect of two dose levels of Ganirelix on LH secretion (mean, basal and total).

**Secondary Objective 2:**
To assess the effect of two dose levels of Ganirelix  on LH variation (mean, basal and total LH) before and after Ganirelix injection will be assessed.

To assess the effect of two dose levels of Ganirelix on androgen production.

**Secondary Objective 3:**
To determine the effect of two dose levels of Ganirelix on variations in follicle-stimulating hormone (FSH), estradiol, and anti-Müllerian hormone (AMH) levels.

# EVALUATION CRITERIA

### ****4.1 Endpoint for the Primary Objective****

The expected decrease in LH pulse frequency before and after Ganirelix* administration is estimated to be between 20% and 30%.
To be considered an LH pulse or peak, the value had to show an increase of more than 20% compared with one of the two preceding points, followed by a decrease of more than 10% in one of the two subsequent points.

### ****4.2 Endpoints for the Secondary Objectives****

**Secondary Endpoint 1:**
The variation in LH secretion before and after Ganirelix injection will be calculated as the mean LH (the average of all LH values over the study period) and basal LH, corresponding to the mean of the five lowest LH values over the study period. The total LH corresponds to the sum of all LH values at T0-T240 and T240-T480.

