### ****7.2 Study Procedures****

This is a **phase 1 pilot study** with **two parallel groups**, evaluating the efficacy of two different doses of Ganirelix in **20 women with PCOS**, defined by **oligo-/anovulation**, **hyperandrogenism**, and **elevated circulating LH levels**.

An **intravenous cannula** will be inserted, and **blood samples will be collected every 10 minutes** for a **4-hour baseline period** starting at 8:00 a.m.
Subsequently, Ganirelix will be administered as a **single subcutaneous injection** at one of two doses:

- **0.025 mg** (n = 10 PCOS patients)
- **0.0625 mg** (n = 10 PCOS patients)

These doses correspond to approximately **one-tenth and one-quarter** of the standard clinical dose used in **IVF protocols** to achieve full LH suppression.

Following Ganirelix administration, blood sampling will continue every 10 minutes for an additional **4-hour period**.

The **primary endpoints** include mean LH levels, as well as LH pulse **frequency and amplitude**, evaluated before and during treatment with Ganirelix.
In healthy women, LH surges occur approximately every 90 minutes during the early follicular phase, whereas **lean women with PCOS** may exhibit **one or more LH pulses per hour**.

The expected outcome is to determine the Ganirelix dose that reduces the **abnormally elevated frequency** of LH pulses by approximately **20–30%**, bringing them closer to normal physiological values.

**Secondary outcomes** include reproductive hormone markers — **serum testosterone, androstenedione, LH, FSH, estradiol, and AMH levels** — measured before treatment and **4 hours post-injection**.

The **pretreatment period** (baseline LH secretion and pulsatility) will be compared to the **4-hour post-antagonist period.**An **LH pulse** will be defined as a **≥20% incremental change** in LH concentration between the nadir and the subsequent peak, as previously described in similar clinical studies (Ref. 25).

The degree of gonadotropin suppression will be calculated as a **percentage of inhibition** relative to the pre-antagonist period:

$$\text{Inhibition (\%)}=\frac{(\text{PRE mean}-\text{nadir})}{\text{PRE mean}}\times100$$

as described previously (Ref. 26).
Hormone nadir levels will be computed using a **moving average**.
For LH, a **6-point moving average** (equivalent to 1 hour of sampling) will be used, as the nadir is expected to occur within the 10-minute sampling intervals.

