**Handling of Missing Data**
Given the short study duration and intensive monitoring, missing data are expected to be minimal. Any missing measurements will be described, and no imputation is planned. Analyses will be based on available data only.

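### Total LH is a raw sum with no scaling for missed samples, so unequal sample loss before and after injection shifts its change by about 4% per sample

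*Protocol*

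**What the plan says.** Section 4.2, Secondary Endpoint 1, names three LH measures to be compared before and after injection. Total LH is defined as follows: "The total LH corresponds to the sum of all LH values at T0-T240 and T240-T480". The synopsis repeats this. Mean LH is an average of all values. The third measure is "basal LH, corresponding to the mean of the five lowest LH values over the study period".

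The Statistical Analyses section, under Handling of Missing Data, gives the rule for missed samples: "Any missing measurements will be described, and no imputation is planned. Analyses will be based on available data only". It adds: "Given the short study duration and intensive monitoring, missing data are expected to be minimal". The protocol states no scaling of the sum, no interpolation and no minimum number of samples per window.

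The same section lists mean, basal and total LH as secondary analyses. It treats all secondary analyses as exploratory and uses a per-protocol population that the protocol does not define further.

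**The concern.** A sum depends on how many values go into it. If a draw is missed and nothing replaces it, the window's total falls even when LH has not changed. The before/after change in total LH then mixes a drug effect with a count of samples. The distortion comes from combining two rules that the protocol itself fixes: the sum, and the use of available data without imputation.

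T240 is the end of the first window and the start of the second, so one sample taken at the time of injection counts as both before and after.

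The protocol says the study is meant to supply preliminary estimates for a later confirmatory trial. With 10 women per dose, a few incomplete profiles can move such an estimate.

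**Working it through.** **Inputs.** Sampling is every 10 minutes for 8 hours, 4 hours before and 4 hours after injection (section 7.2). The Biological Analyses table gives 49 LH tubes of 1.5 mL plus six 5 mL tubes. There are 10 women per dose (section 5.3).

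**Reproducing the protocol's counts.** 480/10 + 1 = 49 samples, which matches. 49 × 1.5 + 6 × 5 = 103.5 mL, which matches the stated blood volume. Each window, read inclusively, holds 240/10 + 1 = 25 samples, and 25 + 25 - 1 = 49, so T240 is shared.

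**Effect of missed samples on total LH.** Assume no drug effect, missed samples at the average level of the window, T240 itself not missed, and change expressed relative to the pre-dose total.

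- k samples lost after injection: (25 - k)/25 - 1 = -k/25
- k samples lost before injection: 25/(25 - k) - 1

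| Samples lost | Lost after injection | Lost before injection |
| --- | --- | --- |
| 1 | -4.0% | +4.2% |
| 2 | -8.0% | +8.7% |
| 3 | -12.0% | +13.6% |
| 5 | -20.0% | +25.0% |
| 7 | -28.0% | +38.9% |

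Equal losses in both windows give 0%. A missed T240 lowers both sums and roughly cancels.

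With a real effect the distortion multiplies. Leaving the shared T240 aside, a true 20% fall with three post-dose samples lost reads as 1 - 0.8 × 22/25 = 29.6%. With three pre-dose samples lost it reads as 1 - 0.8 × 25/22 = 9.1%.

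At group level, one woman in ten losing five post-dose samples moves the mean change by 20/10 = 2 percentage points.

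**Effect of T240 in both windows.** Assume T240 is unaffected by the drug and LH falls by a flat 30% from T250. The post-dose sum is 1 + 24 × 0.7 = 17.8 units against 25, so the fall reads as 1 - 17.8/25 = 28.8%. Removing T240 from the post-dose raw sum, with no other change, would leave 24 terms against 25, a built-in 24/25 - 1 = -4% with no drug effect. Reallocating T240 is therefore safe only once the measure is scaled.

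**Is it confined to total LH?** With complete data, total LH = 25 × mean LH, so the sum carries no information that the mean lacks. A simulation checked how all three measures respond, with mean and basal LH taken within each window. It assumed pulses about hourly, a 60-minute half-life, 5% assay variation and no drug effect, with 6,000 series per pattern. The simulated series drift upward by about 3% even with no loss, so only differences from the no-loss run matter. Mean LH stayed within about 0.3 points of that run in every pattern. Basal LH rose by about 1.2 points when five post-dose samples were lost (5.29 - 4.07), slightly away from suppression.

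**The case against.** The best defence is that this hardly matters. Missing data are expected to be minimal, total LH is exploratory, and the primary endpoint, pulse frequency, does not use the sum. Mean LH is reported beside it, so a distorted total would show as a discrepancy. A 20% artefact needs five of 25 post-dose samples lost and none before. The per-protocol set might exclude incomplete profiles, and an analysis plan not shown here could set a rule for them. The 20-30% target is stated for pulse frequency in section 4.1 and extended to mean and basal LH in the synopsis, but never to total LH. Sharing T240 keeps both sums at 25 terms and only dilutes a true effect.

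Most of this stands, and it limits the importance of the point. It does not remove it. The raw sum and the available-data rule are both written into the protocol, and together they give a wrong result whenever losses are unequal.

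A reader might also infer that the change in basal LH cannot be computed, because its definition refers to the whole study period. The documents do not support that. The same sentence in section 4.2 opens with the variation before and after injection, section 7.2 compares the pretreatment period with the 4 hours after the antagonist, and the analysis section assesses all three measures before and after. The wording is loose, but the intended windows are clear.

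**Conclusion.** The point holds for total LH. Each sample lost from one window without a matching loss from the other shifts the relative change by about 4%: toward apparent suppression if lost after injection, away from it if lost before. The per-sample figures assume missed samples at the window average. Counting T240 twice is a smaller fault, 1.2 points on a true 30% fall, and it works against finding an effect.

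Two stronger readings are tempting. One is that every missed sample looks like drug suppression; the arithmetic contradicts this, since pre-dose losses act the other way and balanced losses cancel. The other is that the error leans toward a false drug effect because a cannula is more likely to fail late in the session. Section 6.3 allows withdrawal for discomfort during the 8 hours, so shortened profiles are possible, but the protocol gives no rate or timing of missed samples and no net direction can be claimed.

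This is a modest correction to an exploratory measure. It is worth making because the distortion is certain whenever losses are unequal and is easily avoided.

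**What to change.** In section 4.2 and the synopsis:

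- Replace the raw sum with a measure scaled to what was observed in each window: a time-weighted mean, that is, the trapezoidal area under the LH curve divided by the observed time span. This handles gaps inside a window.
- State a minimum coverage per window, and say how a profile below it is treated. Dividing by the observed span does not repair a post-dose profile that stops early. The product information in Annex 4 puts peak concentration at 1-2 hours, so a truncated profile gives too much weight to the time before full exposure.
- Assign T240 to the pre-dose window only, so that the post-dose window runs from T250 to T480. Make this change together with the scaling, not on its own.
- As a wording correction, define mean and basal LH within each 4-hour window in place of the reference to the study period.

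The cost is a few sentences in two places, with no new samples or assays. If total LH is kept for comparison with other work, it can be reported as the scaled mean times a fixed window length.

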**Secondary Endpoint 2:**
Variation in androgen production at 4 hours post-injection, defined as the difference between the total testosterone and androstenedione levels measured at H8 (4 hours after injection) and H0 (4 hours before injection).

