| **Intervention description** | An intra-venous cannula will be inserted and blood will be sampled at 10-min intervals for a 4-h baseline period commencing at 0800 h. Ganirelix will be then administered subcutaneously at single-dose regimen at 0.0625 mg (n = 10 women with PCOS). After Ganirelix administration sampling will continue at 10-min intervals for 4 h. |
| **Name of arm 2** | Pilot phase-0, parallel, clinical study.  Test the efficacy of Ganirelix administered subcutaneously at single-dose regimen of 0.025 mg in 10 women with PCOS, in rectifying LH pulse frequency and LH amplitude. |
| **Intervention (at least one intervention)** | Drug (including placebo)  Radiation  Other  Device (including sham) Behavioral  Biological / vaccine  Genetic  Procedure / surgery  Dietary supplement |
| **Intervention name** | Ganirelix (Orgalutran) |
| **Intervention description** | An intra-venous cannula will be inserted and blood will be sampled at 10-min intervals for a 4-h baseline period commencing at 0800 h. Ganirelix will be then administered subcutaneously at single-dose regimen at 0.025 mg (n = 10 women with PCOS). After Ganirelix administration sampling will continue at 10-min intervals for 4 h. |
|  | **Primary Outcome measure** |
| **Title** | Serum LH level every 10 minutes for 8 hours |
| **Time point at which primary outcome measure is assessed** | The degree of gonadotropin suppression will be determined by calculating the percent inhibition from the pre-antagonist period [(mean PRE - nadir)/mean PRE] x 100, where nadir hormone levels will be calculated using a moving average. |
|  | **Secondary outcome measures, repeating as many times as 2nd outcomes** *Noter les 5 principaux critères d’évaluation* |
| **Title** | Measurement of serum testosterone and androstenedione, FSH, estradiol and AMH levels |
| **Time point(s) at which Secondary outcome measure is assessed** | Serum testosterone and androstenedione, FSH, AMH and estradiol levels at the beginning and at the end of the 8 hours |
| **Inclusion criteria** | -women aged 18 to 35  -women with PCOS with AMH> 28 pmol / L, LH> 8 IU / mL and testosteronemia > 0.39 ng/mL  - no hormonal treatment or contraception for 2 months  - women covered by the Social Security system  Non obese women |
| **Exclusion criteria** | -hormonal treatment or hormonal contraception  - Metformin treatment  -pregnant woman  -inability to understand the newsletter |

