**Secondary Endpoint 3:**
Variation in FSH, estradiol, and AMH levels at 4 hours post-injection, defined as the difference between concentrations measured at H8 (4 hours after injection) and H0 (4 hours before injection).

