# METHODOLOGY

### ****5.1 Study Design****

This is a **single-center, phase I pilot study** with **two parallel groups**.

The study will be proposed during endocrinological gynecology consultations to all patients meeting the inclusion criteria. After obtaining written informed consent, participants will be assigned to one of the two dose groups.

During the 4 hours preceding Ganirelix injection*, baseline LH secretion and pulsatility, as well as baseline levels of androgens, FSH, estradiol, and AMH, will be measured.

Subsequently, patients will receive a **low-dose injection of Ganirelix***. LH secretion and pulsatility will be monitored for **4 hours following the injection**, along with measurements of androgens, FSH, estradiol, and AMH at **H8**.

The expected outcome is to identify the Ganirelix* dose that reduces the abnormal frequency of LH pulses in women with PCOS to values comparable to normal conditions (approximately a 30% reduction).

As **secondary outcomes**, reproductive markers (serum levels of testosterone, androstenedione, LH, FSH, estradiol, and AMH) as well as glucose, insulin, and liver function parameters will be assessed before and after the 4-hour GnRH antagonist treatment period.

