### ****7.2.3 Inclusion Visit****

At the inclusion visit, **written informed consent** will be collected, and the **study procedures** will be carried out over a **single study day (8:00 a.m. to 4:00 p.m.)**, scheduled **at the beginning of the menstrual cycle**.

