# BIOLOGICAL ANALYSES

**Routine Clinical Tests and Study-Specific Biological Analyses**

All laboratory analyses will be conducted under the supervision of **[name] [name]**, Department of **Hormonology, Nutrition, and Oncology**, at the**Institute of Biochemistry and Molecular Biology**, within the **Biology, Pathology, and Genetics Division** of **Lille University Hospital (CHU de Lille).**

| **Parameters to be Analyzed** | **Baseline (T0)** | **Intermediate Time Points (every 10 min for 8 h)** | **Final Time Point (T0 + 8 h)** | **Use (Clinical/Research)** | **Location & Responsible Unit** |
| --- | --- | --- | --- | --- | --- |
| LH | — | 1 dry tube (1.5 mL) at each time point | — | Research | CBP Biochemistry Laboratory |
| LH, FSH, Estradiol, Total Testosterone | 1 dry tube (5 mL) | — | 1 dry tube (5 mL) | Research | CBP Biochemistry Laboratory |
| AMH | 1 dry tube (5 mL) | — | 1 dry tube (5 mL) | Research | CBP Biochemistry Laboratory |
| Androstenedione | 1 dry tube (5 mL) | — | 1 dry tube (5 mL) | Research | CBP Biochemistry Laboratory |
| **Total** | **3 dry tubes (5 mL)** | **49 dry tubes (1.5 mL)** | **3 dry tubes (5 mL)** | **Research** | **CBP Biochemistry Laboratory** |

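### The androgen, FSH, estradiol and AMH changes presented as four-hour post-injection changes start from a sample taken four hours before the injection, so half of the interval is untreated

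*Protocol*

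**What the plan says.** Protocol section 4.2 presents secondary endpoint 2 (total testosterone and androstenedione) as a change four hours after injection and defines it as the difference between "levels measured at H8 (4 hours after injection) and H0 (4 hours before injection"). Secondary endpoint 3 (FSH, estradiol, AMH) is likewise "defined as the difference between concentrations measured at H8 (4 hours after injection) and H0 (4 hours before injection"). The synopsis uses the same two time points.

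The clock times come from elsewhere. The ClinicalTrials.gov synopsis has sampling every 10 minutes "for a 4-h baseline period commencing at 0800 h", followed by the injection and four more hours of sampling. Section 7.2.3 describes a "single study day (8:00 a.m. to 4:00 p.m").

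The table under Biological Analyses, repeated in Annexe 3, gives these hormones a tube at baseline and a tube at T0 + 8 h, with nothing between: "LH, FSH, Estradiol, Total Testosterone | 1 dry tube (5 mL) | — | 1 dry tube (5 mL"). AMH and androstenedione have the same pattern. Only LH is drawn every 10 minutes.

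The Secondary Endpoint Analyses paragraph compares H0 with H8 and interprets the FSH, estradiol and AMH differences as changes following treatment. It labels the androgen difference as post- versus pre-injection. Section 5.2 names each woman as her own control, and section 5.2.1 gives ganirelix to all 20 women in two consecutive dose groups of 10.

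**The concern.** A within-woman comparison isolates a treatment effect only if the control value describes her state when treatment starts. Here it describes her state four hours earlier. A drug effect has four hours to appear, while anything else that moves the hormone during the day (time of day, or the study procedure itself) has eight. With no untreated group, the data cannot separate the two.

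The protocol avoids this for LH: secondary endpoint 1 sets T0-T240 against T240-T480, on either side of the injection. It gives no reason for treating the other hormones differently.

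At stake is how two results will be read. One is whether a low dose lowers androgens. The other is whether FSH and estradiol are preserved, which bears on the stated aim of not suppressing the reproductive axis. Drift in one direction could imitate an effect; drift in the other could hide one.

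**Working it through.** **Timeline.** Inputs: start at 08:00 (section 7.2 and the registration synopsis), four untreated hours, end at 16:00 (section 7.2.3).

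- H0 = 08:00
- Injection = 08:00 + 4 h = about 12:00
- H8 = 08:00 + 8 h = 16:00
- Untreated share of H0 to H8 = 4 / 8 = 50%

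This agrees with the protocol's own placing of H0 and H8 four hours either side of the injection.

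**Is there another value to use?** No. In the sampling tables FSH, estradiol and total testosterone share one tube, and AMH and androstenedione have one each, all at T0 and T0 + 8 h only. No planned measurement marks the start of exposure.

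**Size of the effect.** The protocol gives no drift rate, so the rates below are assumptions. Let e be the true proportional fall due to drug, d the hourly fall unrelated to drug, and h the hours from baseline to H8:

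apparent fall = 1 − (1 − e)(1 − d)^h, with h = 8 from H0 and h = 4 from T240.

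| Assumed d per hour | No drug effect, from H0 | No drug effect, from T240 | True 20% fall, from H0 | True 20% fall, from T240 |
| --- | --- | --- | --- | --- |
| 0.5% | 3.9% | 2.0% | 23.1% | 21.6% |
| 1% | 7.7% | 3.9% | 26.2% | 23.2% |
| 2% | 14.9% | 7.8% | 31.9% | 26.2% |
| 3% | 21.6% | 11.5% | 37.3% | 29.2% |

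Example: 1 − 0.98^8 = 14.9%; 1 − 0.98^4 = 7.8%.

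A rise works the other way. With +2% per hour and a true 20% fall, H0 gives 1 − 0.80 × 1.02^8 = 6.3%, and T240 gives 1 − 0.80 × 1.02^4 = 13.4%. A T240 baseline roughly halves the contamination; it does not remove it.

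**Feasibility of a T240 sample.** Section 7.2 states that "An intravenous cannula will be inserted" for the 10-minute sampling. Draws from 0 to 480 minutes number 480 / 10 + 1 = 49, which matches the 49 LH tubes, so a draw at T240 is already planned.

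- Present volume: 49 × 1.5 + 6 × 5 = 103.5 mL, the protocol's figure
- Three tubes moved from T0 to T240: still 103.5 mL
- Three tubes added at T240: 103.5 + 15 = 118.5 mL

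Annexe 2 allows 102 mL per session at 51 kg, the minimum weight in section 6.1 (2.5% of 4,080 mL). That favours moving the tubes over adding them. The present 103.5 mL is itself above 102 mL at exactly 51 kg, a separate mismatch to be reconciled.

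**The case against.** The H0/H8 design is stated openly and almost uniformly, and nothing in the protocol suggests that these hormones drift, by how much or in which direction. That stands: the table illustrates what an assumed rate would do and is not an estimate. No case is made here that all five hormones drift. The structural point, a half-untreated interval without an untreated control, needs no rate.

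The stakes are also limited. The protocol calls all secondary analyses exploratory and disclaims formal hypothesis testing. The primary LH endpoint is not touched, because LH is sampled on both sides of the injection. This stands too.

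Three stronger readings may tempt a reader, and the protocol does not support them:

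- **That section 5.1 is contradicted.** It has the markers assessed "before and after the 4-hour GnRH antagonist treatment period". H0 does lie before that period, and the same section places baseline measurement within the four hours preceding injection. The baseline is badly placed, not inconsistent with 5.1.
- **That drift alone could meet the trial's androgen criterion.** The 20-30% androgen reduction is a goal in the synopsis rationale; endpoint 2 has no threshold. A 20% fall from drift alone would need about 2.75% per hour compounded (1 − 0.80^(1/8)), and no such rate is documented.
- **That all drift is necessarily credited to the drug.** The only tests named are unpaired. If they compare H8 − H0 changes between doses, drift common to both groups cancels in expectation, subject to the groups being consecutive and not randomised. The problem lies in the within-woman reading, and a between-dose comparison cannot show that either dose changes a hormone from its untreated level.

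**Conclusion.** The point holds as a cheap improvement to a design choice. Endpoints 2 and 3 are presented as four-hour post-injection changes but span eight hours, four of them before any drug, with no untreated group. Under assumed non-drug falls of 0.5 to 3% per hour, compounded and with no drug effect, the H0-based change would show 3.9 to 21.6%, against 2.0 to 11.5% from T240. The 50% untreated share follows from the protocol's own times; the percentages rest wholly on the assumed rates, and drift could equally go the other way.

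A reader might infer that a T240 baseline makes the change attributable to ganirelix. It does not: the 12:00-16:00 part remains confounded. The effect is confined to secondary, exploratory endpoints.

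**What to change.** Draw the three 5 mL tubes at T240, immediately before the injection, instead of at T0, and define secondary endpoints 2 and 3 as H8 minus H4. Make the edit everywhere the H0 baseline appears:

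- the full synopsis (experimental plan, secondary objective 3, secondary endpoints 2 and 3, statistical analysis plan row)
- the ClinicalTrials.gov synopsis, secondary outcome timing
- section 4.2, secondary endpoints 2 and 3
- the sampling tables under Biological Analyses and in Annexe 3
- Statistical Analyses, Secondary Endpoint Analyses

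In the analysis section, add that the remaining 12:00-16:00 change cannot be separated from drug effect, so the within-woman change is descriptive.

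The cost is a protocol amendment. The number of tubes, the volume (103.5 mL) and the procedures stay the same, and the T0 LH value is still supplied by the 10-minute series. The downside is losing the 08:00 reference value for the other hormones. Keeping both baselines would take the total to 118.5 mL, which would have to be reconciled with Annexe 2.
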